## Abstract

**Background:**

With the increasing amount of geriatric surgery, it has become a great challenge for anesthesiologists to reduce the incidence of postoperative pulmonary complications (PPCs). The two most popular airway management methods, laryngeal mask airway (LMA) and endotracheal intubation (ETI), both have their unique advantages in specific clinical settings. For the purpose of helping clinicians make better decisions on airway management during geriatric surgery, we designed this multi-center clinical trial to compare the influence of LMA and ETI on PPCs.

**Methods/design:**

In this multi-center, randomized, parallel clinical trial, a total of 6000 elderly patients, aged ≥ 70 years, with an American Society of Anesthesiologists classification level of 1–2 and a body mass index ≤ 35 kg/m^2^, undergoing elective surgery will be enrolled and randomized into the LMA or the ETI group. Both groups will receive usual perioperative care except for the adoption of LMA/ETI. Primary outcomes are the occurrence of PPCs and patients’ perioperative mortality rates. Ease of intubation, anesthetics consumption, treatment for PPCs, duration of surgery, anesthesia recovery time and performance, time of PPC onset, postanesthesia care unit stay, intensive care unit admission and stay, in-hospital days, re-admission rates, hospitalization cost, and patients’ satisfactory scores will be secondary outcomes. Follow-up will be conducted through phone-call visits until 12 weeks after discharge.

**Discussion:**

This trial will assess the possible benefits or disadvantages of perioperative LMA use in elderly patients compared with ETI regarding the occurrence of PPCs and clinical prognosis. We expect that this trial will also add to the current understanding of PPCs in geriatric populations and contribute to the international recommendations of geriatric surgery management.

**Trial registration:**

ClinicalTrials.gov, NCT02240901. Registered on 16 September 2014.

**Electronic supplementary material:**

The online version of this article (10.1186/s13063-019-3351-2) contains supplementary material, which is available to authorized users.

## Background

Aging is an astonishing demographic transformation faced by the modern world. According to the United Nations, the number of elderly persons will triple over the next 50 years [1]. In China, life expectancy is now > 75 years [2], and by 2050, there will be 100 million people aged older than 80 years [3]. Undoubtedly, along with the increased longevity, the incidence of geriatric surgery will greatly increase, thus posing more challenges in perioperative care for clinical practitioners.

The aging population is a frail group because aging is associated with degenerative changes in anatomical structure, reduced functional tolerance, altered pharmacokinetics, and a higher incidence of morbidity and mortality [4–6]. Cardiovascular, pulmonary, and neurologic complications are the three most common postoperative complications in this population [5]. A postoperative pulmonary complication (PPC), although its definition is still in inadequate consensus, is generally accepted as a clinical measure that encompasses a wide range of postsurgical respiratory outcomes, including pneumonia, atelectasis, and systemic inflammatory response syndrome (SIRS). The incidence of PPCs may vary in different surgery types, with a reported incidence ranging from 1 to 23% [7].

Among numerous risk factors for the development of PPCs, aging is a well-accepted and independent one [7, 8]. Even when the patient is free from respiratory co-morbidity and does not show any evident physical decline before surgery, PPCs can still be triggered by an episode of severe incidence such as surgery and anesthesia [7]. Multiple studies have suggested that patients aged > 60 or 65 years are at higher risk of developing PPCs, and the risk increases with increased age [9, 10]. Other risk factors for developing PPCs include smoking, obesity, pulmonary co-morbidities, positive cough test, prolonged surgery time, limited laryngeal height, and extended forced expiratory time [11, 12].

Geriatric patients often have limited mouth opening and cervical movement, poor cardiovascular tolerance, and altered pharmacokinetics. Under these circumstances [5], a laryngeal mask airway (LMA) is considered a good alternative to endotracheal intubation (ETI) because of its advantageous characteristics such as ease of insertion [13], less irritation to the airway, less reliance on muscle relaxant, and better patient comfort [14]. As a supraglottic airway device, however, it does not separate the trachea from the esophagus; therefore, the LMA is associated with higher incidence of aspiration of gastric contents, especially in susceptible patients with a history of gastroesophageal reflux disease [15]. Moreover, the LMA is not recommended for use in lengthy surgery, morbidly obese patients, or certain other types of surgeries in which more control of the breathing (e.g., heart, lung, and brain surgeries) [16] is required. Therefore, the LMA and ETI both have major roles in daily anesthetic practice, and their influences on PPCs under various circumstances are inevitable topics for question.

In contrast to the popularity of LMA or ETI usage in geriatric surgeries, research evidence about their effect on PPCs is scarce and incomprehensive. Our group published a retrospective single-center study that compared LMA and ETI use in geriatric patients who underwent elective abdominal surgery, and we found that, among those who were transferred into the intensive care unit (ICU), the LMA group was associated with lower incidence of atelectasis and pulmonary embolism [17]. To better clarify whether the use of LMA is superior to ETI for elderly surgical patients and provide sufficient evidence for clinical decision-making, we have designed the current large-scale, randomized, controlled clinical trial. Its rationale, design, and protocol will be described in this paper.

## Methods/design

### Study settings

The effectiveness and pulmonary complications of perioperative LMA used in elderly patients (POLMA-EP) study is an ongoing, multi-center, randomized, controlled clinical trial with the aim of comparing the effects of the LMA and ETI on PPCs in elderly patients. This trial is registered at ClinicalTrial.gov with ID number NCT02240901. The trial flow chart is shown in Fig. 1. This protocol is in accordance with the Standard Protocol Items: Recommendations for Interventional Trials (SPIRIT) guidelines (see Additional file 1).

**Fig. 1 Fig1:**
[figure not shown]
Study flow diagram

We plan to recruit more than 6000 patients from 17 clinical centers in China. The participating clinical centers are listed in Table 1.

**Table 1 Tab1:** POLMA-EP research clinical centers

Site ID	Site name
1	Ren Ji Hospital (East), affiliated to Shanghai Jiao Tong University School of Medicine
2	Fudan University Shanghai Cancer Center
3	Shanghai Changzheng Hospital
4	Shanghai First Maternity and Infant Hospital
5	Huadong Hospital, Fudan University
6	West China Hospital, Sichuan University
7	Shanghai Guanghua Hospital of Integrated Traditional Chinese and Western Medicine
8	Shanghai Jiading District Central Hospital
9	Shanghai Pudong District Central Hospital
10	Shanghai Huangpu District Central Hospital
11	Shanghai Fengxian District Central Hospital
12	Ren Ji Hospital (West), affiliated to Shanghai Jiao Tong University School of Medicine
13	People’s Hospital of Pudong New District, Shanghai
14	Ren Ji Hospital (South), affiliated to Shanghai Jiao Tong University School of Medicine
15	First Affiliated Hospital of Wenzhou Medical University, Zhejiang Province
16	The Second People’s Hospital of Wuxi, Jiangsu Province
17	First Affiliated Hospital of Xiamen University, School of Medicine

### Inclusion and exclusion criteria

The inclusion criteria are as follows: (1) age ≥ 70 years, (2) elective surgery, (3) American Society of Anesthesiologists (ASA) classification I–II, (4) body mass index (BMI) ≤ 35 kg/m^2^, (5) provision of signed informed consent.

The exclusion criteria include patients who (1) require emergency surgery; (2) have anticipated difficult intubation; (3) have a broken or unstable cervix; (4) have laryngeal disease; (5) are at high risk of aspiration (gastroesophageal reflux disease, full stomach); (6) are unable to cooperate for any reason, such as inability to speak or understand, mental disease, or inability to go to the clinics; (7) have taken experimental drugs in the preceding 3 months or joined another clinical trial; (8) did not provide informed consent or have withdrawn consent; (9) are evaluated by the investigators as unsuitable for this trial.

### Ethics issues

This study is approved by the Ethics Committee of Ren Ji Hospital, Shanghai Jiao Tong University School of Medicine. Surgery will be performed within 2 weeks after the screening process. Designated doctors will explain this trial to interested potential participants in detail and provide them with the informed consent form. Participants are given at least 24 h to decide whether they wish to participate in this trial. The informed consent form will be signed by the participant or his/her trustee or guardian and may be withdrawn at any time during the trial. Written informed consent and the patient’s baseline data will be obtained before randomization. Moreover, participants are encouraged to contact the research team if they have any health concerns during the trial.

### Blinding, randomization, and allocation concealment

Given the nature of the intervention, blinding of caregivers or patients is not possible. However, investigators responsible for data collection and statisticians will be blinded to the study arms.

Random numbers and group allocations are generated with a 1:1 ratio and stratified according to PPC risk scores (listed in Table 2) by a central randomization system known as an interactive web response system (IWRS) developed by Beijing Blue Balloons Technology Company Limited (http://www.blueballon.cn). Allocations generated by the IWRS will be stored in opaque and numbered envelopes. Participants will be given a randomization number by the designated anesthesiologist and will be allocated according to indications inside that numbered envelope. If participants decide to withdraw after assignment, their clinical information will not be used in this trial, but their assigned random number will still be retained.

**Table 2 Tab2:** PPC risk index

Independent risk factors	Risk score
Age > 70 years	1
Cough and sputum production	1
Diabetes	1
Smoker (or patient quit within the past 6 months)	1
COPD	1
BMI > 27 kg/m^2^	1
FEV1 < 80% and FEV1/FVC < 70%	2

*COPD* chronic obstructive pulmonary disease, *BMI* body mass index, *FEV1* forced expiratory volume in 1 s, *FVC* forced vital capacity

In emergent cases when the LMA or the ETI tube cannot be placed successfully after multiple attempts, anesthesiologists may change the ventilation method or administer different treatments according to their best clinical judgement, and the patient will be excluded from the trial.

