**Fig. 2 Fig2:**
[figure not shown]
Standard Protocol Items: Recommendations for Interventional Trials (SPIRIT) figure for the POLMA-EP trial

Upon arrival, a series of baseline information will be collected, including the patient’s demographics, cause of hospitalization, elective surgery type, medical history, anaphylactic history, and co-morbidities and concomitant medication. Physiological parameters will also be collected, including blood pressure (BP), heart rate (HR), respiratory rate (RR), core body temperature (or axillary temperature + 0.5), ASA classification level, and risk for PPCs. The patient’s cardiovascular, neurological, respiratory, endocrine, and urinary functions will be evaluated and recorded. Laboratory tests including routine blood test, blood gas analysis, and pulmonary function indicators such as vital capacity (VC), forced vital capacity (FVC), forced expiratory volume in 1 s (FEV1), and peak expiratory flow (PEF) will also be measured and documented.

On the day of surgery, anesthetic and surgical recording will also be completed. This will include anesthesia type and duration, mechanical ventilation length, surgery time, PACU stay, blood products (red blood cells/plasma/platelets/fresh frozen plasma/albumin) transfusion, fluid infusion (crystalloid solution and artificial colloids), amount of bleeding, intubation type, times of attempts, ventilation mode, positive end-expiratory pressure (PEEP), tidal volume, types and dosage of anesthetic drugs, and ICU admission and stay.

The PPC level, routine blood tests, blood biochemistry, and blood gas analysis of each patient are evaluated at days 1, 3, and 7 and before discharge. Before discharge, important examinations such as pulmonary radiography and sputum and blood cultures will be completed and recorded. For PPCs, treatments including medication (drug name and dose) and mechanical ventilation (mode, duration, and other parameters) will be documented. In cases of death, the time, cause, and relativity to surgery or anesthesia will be evaluated and recorded.

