There are several noteworthy limitations of this study. Firstly, all participating centers are located in east China; therefore, one may not postulate that results from this study can be implemented directly to other places or populations. Secondly, the long-term follow-up results are mainly based on patients’ self-evaluated questionnaires, which potentially can add bias to the results of this study. Thirdly, we are unable to apply uniform treatment to all patients. The ventilation mode adopted during anesthesia, administration of analgesics, and the prophylactic use of antibiotics, anticholinergics, and steroids are decided according to clinicians’ best judgement and will be recorded for future subgroup analysis. Other potential confounding factors [20], including surgery type and duration, will also be evaluated during statistical analysis. Moreover, the LMA device has many different forms and configurations. In this study, it is unreasonable to designate a single type of LMA device, but the mode of LMA used will be recorded. Lastly, the patient is not blinded in this trial, because extubation criteria need to be met before the LMA or the ETI tube can be removed. Even though we will make sure that every participant is informed not to reveal his/her group allocation to assessors, there is still the risk of assessor unblinding. In such cases, the patient will be evaluated by another assessor.

With our multi-center, randomized, controlled study, we aim to evaluate the safety profile of LMA/ETI use and add to the knowledge pool of airway management in elderly patients. The findings from this study can be used to help with clinicians’ understanding of the issue and can be used in clinical settings when decisions need to be made.

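### The stratification score barely registers age in this population and has no surgery item, and the named test for PPC incidence adjusts for neither: a modest loss of precision, not a bias

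*Protocol article*

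**What the plan says.** In the section on blinding, randomization and allocation concealment, 1:1 allocation is "stratified according to PPC risk scores (listed in Table 2"). No other stratification factor is named. Table 2 has seven items: age above 70, cough and sputum, diabetes, smoking, COPD, BMI above 27, and reduced FEV1 with reduced FEV1/FVC.

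Eligibility reads: "The inclusion criteria are as follows: (1) age ≥ 70 years, (2) elective surgery".

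The Background says of ageing as a risk factor that "aging is a well-accepted and independent one" and that "the risk increases with increased age". On surgery it says: "The incidence of PPCs may vary in different surgery types, with a reported incidence ranging from 1 to 23"%. It also lists smoking, obesity, pulmonary co-morbidity, a positive cough test and long surgery time, among others.

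The baseline record in Data collection and follow-up includes demographics and "elective surgery type". The Ethics issues section says that baseline data are obtained before randomization.

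The Statistical analysis section names χ² and Fisher's exact tests for proportions, and a logistic model to look for confounders, with no covariates listed. The Discussion adds that other potential confounders, "including surgery type and duration, will also be evaluated during statistical analysis".

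**The concern.** Stratifying on a risk score is meant to make the arms alike in PPC risk and to supply a natural adjustment variable. Here one item of the score hardly varies among eligible patients: a 71-year-old and a 95-year-old receive the same point. The age gradient that the Background describes cannot appear in the score. Surgery type does not appear in it at all, although any elective operation is eligible and the article itself ties PPC incidence to the type of operation.

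Even an analysis stratified by the Table 2 score would therefore leave out most of the age information and all of the surgery information. Both are on the baseline record before allocation. If the primary comparison is the plain χ² test, that prognostic information stays in the error term. If adjustment is chosen later under the open promise to evaluate confounders, the choice of covariates is not fixed in advance. At stake are some precision and some protection against post hoc model choice.

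**Working it through.** No figure in the article needs reproducing on this point. The check sets the text side by side and then sizes the consequence.

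**1. The age item.** Eligible: age 70 or more. Scored: age above 70. In completed years, only patients aged exactly 70 miss the point. The article gives no age distribution. Assume that years above 70 are geometric with mean m. The share aged exactly 70 is then 1/(1+m): 1/5 = 20% for m = 4 and 1/9 = 11% for m = 8. A flatter assumption of 3 to 15% is also plausible. Overall, 80 to 97% of patients get the point. If age is taken to the day, almost all do.

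**2. Variance explained by surgery type.** Assume three equal groups averaging the planned control risk of 15%, within the quoted 1 to 23%. R² = Var(pᵢ)/[p(1−p)], with p(1−p) = 0.15 × 0.85 = 0.1275.
- Risks 7/15/23%: variance (0.08² + 0 + 0.08²)/3 = 0.00427; R² = 3.3%.
- Risks 1/21/23%: variance (0.14² + 0.06² + 0.08²)/3 = 0.00987; R² = 7.7%.

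Evaluable patients: 6000 × 0.9 = 5400. Equivalent patients = 5400 × R²/(1−R²), which is about 187 and 453.

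**3. Variance explained by age.** Same geometric form, mean risk 12.5%, assumed odds ratio of 1.5 to 2.0 per 10 years, intercept solved numerically. At mean age 75, R² is 0.8 to 2.6% (41 to 145 equivalent patients). It is sensitive to the tail: 0.5 to 1.6% at mean age 74 and 2.1 to 6.9% at mean age 78.

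**4. Chance imbalance.** Take an extreme two-class surgery factor, 1% versus 23% risk, half the patients in each class, 2700 per arm. The standard error of the difference in class share is √(2 × 0.5 × 0.5/2700) = 1.36 points, so the 95% range is ±2.67 points. Multiplied by the 22-point risk gap, this moves the PPC difference by at most ±0.59 points, against a planned 5. For age, the assumptions in step 3 give about ±0.1 to ±0.5 points.

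**5. Power and type I error.** Simulated with 2700 per arm, two-sided 0.05, 20,000 runs (Monte Carlo standard error about 0.3 points for power at odds ratio 0.80). The crude two-proportion test is compared with a Cochran-Mantel-Haenszel test stratified by surgery type.

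| Surgery mix | Odds ratio | Crude | Stratified |
|---|---|---|---|
| 7/15/23% | 1.00 | 5.1% | 5.2% |
| 1/21/23% | 1.00 | 5.0% | 5.0% |
| 7/15/23% | 0.80 | 78.0% | 79.1% |
| 1/21/23% | 0.80 | 74.9% | 78.0% |
| both | 0.63 | above 99.9% | above 99.9% |

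The planned 15% to 10% is (0.10/0.90)/(0.15/0.85) = 0.63. An odds ratio of 0.80 is not in the article. It takes 15% to about 12.5%, half the planned effect, and is used only to show where precision would matter.

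**The case against.** Several stronger readings are tempting, and the documents do not support them.

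- *The arms will be unbalanced or the result biased.* Random 1:1 allocation of 6000 patients balances age and surgery type in expectation. Step 4 shows that chance imbalance is small against 5 points, and step 5 shows that the crude test keeps its level. Stratification is not needed for validity.
- *Age and surgery type are not used at all.* The Discussion says that surgery type and duration will be evaluated, and the logistic model is open to any confounder. Age is not named there, but it is not shut out.
- *The score misses the main risk drivers.* The article ranks no risk factors. Smoking, obesity, pulmonary disease and cough are all named in the Background and have counterparts in Table 2. The 1 to 23% is a literature range across operations, not a forecast for elective ASA I–II patients in this trial.

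It is also fair to say that a near-constant item does no harm to balance on the other six, that the choice of stratifiers is partly judgement, and that covariate lists are usually left to the analysis plan. The last point carries less weight here. The article does fix a test for proportions, and that test is unadjusted. Adjusting for strong baseline factors already on the record is a better method, not a missing detail. What stands of the objection is the size: at the planned effect nothing material is lost.

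**Conclusion.** The point holds as a modest matter of precision and prespecification. Two facts are plain from the text and need no assumption: the age item hardly varies among eligible patients, and the score contains no surgery item. The stated test for PPC incidence makes up for neither.

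The size does rest on assumptions, since the article gives neither an age distribution nor a surgery mix. Surgery type explains about 3 to 8% of the outcome variance in the two three-group mixes and age probably less, depending on the age tail. The power gain from using surgery type is about 1 to 3 points if the true effect is about half the planned one, and negligible if it is as planned. Neither bias nor inflated type I error follows.

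**What to change.** Keep all allocations made so far. For the primary PPC comparison, prespecify a logistic model with treatment, the stratification score, age as a continuous term, and planned surgery type from the baseline form. Use a short list of surgery categories, fixed and coded before unblinding. Report the standardised risk difference from that model with its confidence interval, together with the conditional odds ratio. The unadjusted χ² result can stay as a supporting analysis.

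Use planned surgery type here, not surgery duration. Duration is known only after allocation and is itself listed among the secondary outcomes.

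The cost is one paragraph of analysis text and one category list, with no new data. At an average risk of 12.5%, 5400 evaluable patients give about 675 events (5400 × 0.125), ample for a few covariates. The one drawback is that the adjusted odds ratio is conditional and differs from the crude one, which is why the risk difference should be reported beside it.

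Replacing the age item by bands that vary above 70 for patients still to be randomised is optional. With allocations stored in numbered envelopes and recruitment under way, it may not be worth the disruption, and the fix does not need it.

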### Secondary outcomes

Secondary outcomes include ease of intubation (number of intubation attempts, disturbance to the following gastric tube insertion), anesthetics consumption, treatment for PPCs, duration of surgery, anesthesia recovery time and performance, time of PPC onset, postanesthesia care unit (PACU) stay, ICU admission and stay, re-admission rate, in-hospital days, hospitalization cost, and patients’ satisfactory score.

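### Randomised patients in whom the assigned airway device cannot be placed are excluded from the trial, so PPCs and mortality are no longer compared between the randomised groups; the direction and size of any bias are unknown

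*Protocol article*

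**What the plan says.** The rules stand in the protocol article under Blinding, randomization, and allocation concealment. Allocations are "generated with a 1:1 ratio and stratified according to PPC risk scores", and each patient receives the device named in a numbered envelope. The last paragraph of the section deals with emergent cases "when the LMA or the ETI tube cannot be placed successfully after multiple attempts". The anesthesiologist may then change the ventilation method or treat differently "according to their best clinical judgement, and the patient will be excluded from the trial".

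A second rule in the same section reads: "If participants decide to withdraw after assignment, their clinical information will not be used in this trial". Only the random number is kept. Under Ethics issues, consent "may be withdrawn at any time during the trial", and the exclusion criteria list patients who "did not provide informed consent or have withdrawn consent" without limiting this to the time before randomisation.

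The section also states that "blinding of caregivers or patients is not possible". The primary outcomes are PPC incidence and perioperative mortality. The secondary outcomes include "ease of intubation (number of intubation attempts, disturbance to the following gastric tube insertion". The Statistical analysis section names no analysis set that would restore the excluded patients.

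**The concern.** Failed placement comes after randomisation and is partly a result of the assigned device. Randomisation therefore does not balance it between arms. How many attempts are made, and when the method is changed, is a judgement made by someone who knows the arm. Removing these patients leaves two groups selected by success with two different devices.

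Three things are at stake.

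- **The question.** A clinician choosing between LMA and ETI needs the outcome of that choice, including what happens when the device cannot be placed. After the exclusion, the trial answers only for successful placements.
- **Both primary outcomes.** The exclusion applies to mortality as well as to PPCs.
- **The attempts outcome.** The patients with final failure are lost from the count of attempts, so its upper end is cut off.

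This is more than silence that a later analysis plan could fill. The text orders the exclusion, and if excluded patients are not followed, their outcomes cannot be recovered.

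**Working it through.** The article gives no failure rate, no PPC risk after failure and no estimate of the bias, so there is no plan figure to reproduce. The check asks how large a false difference the exclusion could create.

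**Inputs from the article**
- PPC incidence 15%, the higher of the two planning rates (15% and 10%), and 3000 patients per group (Sample size estimations).
- Attrition 10%, so 3000 × 0.90 = 2700 per arm as a lower figure.
- Significance level: Statistical analysis gives both 0.05 and 0.025 when two χ² tests are performed. There are two primary outcomes, so both levels are shown.

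**Assumptions (not in the article)**
- Failure *f*: 5% in one arm and 1% in the other, in either direction.
- PPC risk after failure *r*: 15% to 50%.
- No true difference between the arms as randomised: *p* = 0.15 in both.

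**Formula.** Rate seen after excluding failures = (p − f·r)/(1 − f).

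**Worked case, r = 0.35**
- Arm with 5% failure: (0.15 − 0.05 × 0.35)/0.95 = 0.1325/0.95 = 13.95%, with 2850 analysed.
- Arm with 1% failure: (0.15 − 0.01 × 0.35)/0.99 = 0.1465/0.99 = 14.80%, with 2970 analysed.
- Spurious difference: 0.85 points, favouring the arm that fails more often.
- Pooled rate 0.1438; standard error √[0.1438 × 0.8562 × (1/2850 + 1/2970)] = 0.0092; shift 0.0085/0.0092 = 0.925 standard errors.
- Rejection probability at 0.05: Φ(−1.96 + 0.925) + Φ(−1.96 − 0.925) = 15.2%. At 0.025, with critical value 2.241, it is 9.5%.

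**Range, failure 5% versus 1%, 3000 randomised per arm**

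| PPC risk after failure | Spurious difference (points) | Type I error, alpha 0.05 | Type I error, alpha 0.025 |
|---|---|---|---|
| 15% (average risk) | 0 | 5.0% | 2.5% |
| 25% | 0.43 | 7.4% | 4.1% |
| 35% | 0.85 | 15.2% | 9.5% |
| 50% | 1.49 | 37% | 27% |

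Exchanging the two failure rates gives the same figures with the opposite sign. With 2700 per arm, the 35% row becomes 14.2% and 8.7%. With rarer failure (2% versus 0.5%) and 25% risk, the difference is 0.15 points and type I error at 0.05 is 5.3%. With equal failure rates and equal risk after failure, the bias is exactly 0.

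**The other construction.** The table holds the overall rates equal, which requires the arm that fails more often to do better among successful placements. Suppose instead that successful placements have 15% risk in both arms and failures 35%:
- Arm with 5% failure: 0.95 × 0.15 + 0.05 × 0.35 = 16.0%.
- Arm with 1% failure: 0.99 × 0.15 + 0.01 × 0.35 = 15.2%.

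The arms as randomised truly differ by 0.8 points, and the analysis after exclusion expects 15% against 15%. Here the exclusion hides a real difference and creates no false one.

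**The case against.** The strongest objections concern the size and direction of the effect.

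- **Direction.** A reader might infer that the rule favours the LMA. The article does not support that. Its Background section lists easy insertion among the LMA's advantages. If tubes fail more often and failures carry raised risk, the exclusion works against the LMA.
- **Certainty.** A reader might infer that the primary result is bound to be biased and type I error bound to rise. Both require unequal failure (or unequal risk after failure) and above-average risk among failures. The article states neither, and zero bias is possible.
- **Frequency.** The rule is worded for emergent cases. The exclusion criteria already remove anticipated difficult intubation, laryngeal disease and an unstable cervix, so failures may be few. That lowers the likely impact but does not repair the rule.
- **Attempts outcome.** A reader might say this outcome is defeated. It is only truncated: patients placed at a second or later attempt remain.
- **Withdrawals.** Not using data after consent is withdrawn can be an ethical or consent condition, and the consent form is not shown. No withdrawal rate or direction is given, so this rule cannot carry the same weight as the device-failure exclusion.

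All of these stand as limits on what can be claimed. None answers the main point: the exclusion is stated outright, follows allocation and is not reversed elsewhere in the article. Excluding the failures also removes the means of showing that it was harmless.

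**Conclusion.** The defect is real. As written, the plan removes randomised patients because of an event that depends on the assigned device, by a decision taken with the arm known. Neither primary outcome is then compared between the groups that were randomised.

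The size is conditional. Under the stated assumptions it runs from nothing to about 1.5 points in either direction, against a planned difference of 5 points (15% to 10%). A larger sample does not remove such a bias; at a fixed bias it makes a false positive more likely. Depending on how risk is distributed, the exclusion may create a false difference or conceal a true one. The documents do not support a claim about which device gains. Discarding the data of patients who withdraw is a secondary remark, with no magnitude attached.

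**What to change.** Replace the exclusion with wording such as: *All randomised patients are followed for PPCs and mortality and analysed in the arm assigned, whatever airway was finally used. Placement failure and conversion are reported as outcomes. Patients with successful placement of the assigned device form a per-protocol sensitivity set.* The anesthesiologist's freedom to change the airway stays exactly as it is.

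As a secondary change, for withdrawals after assignment, keep the data collected up to withdrawal where consent and ethics terms allow and the patient does not ask for deletion. Report withdrawals by arm.

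The cost is a change of wording and continued follow-up of what should be a small number of converted patients. The estimate may move in either direction. The article says that recruitment is still under way, so the change should be made while follow-up of these patients can still be secured.
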